### Process evaluation

Informed by Proctor et al.’s [27] taxonomy on implementation outcomes, the process evaluation will utilize both qualitative and quantitative methods to assess the key processes of the MIAF. These include implementation fidelity, which measures how closely the MIAF was adhered to as per the original protocol or the intentions of the developers. Feasibility will also be evaluated, gauging the extent to which the MIAF can be effectively implemented within the targeted agencies or settings. Additionally, acceptability will be assessed, focusing on stakeholders’ perceptions of the MIAF’s satisfaction and suitability. Furthermore, the process evaluation will identify enablers and barriers influencing the implementation of each key process within the MIAF. The participants will include caseworkers, foster families, and children in care.

#### Process evaluation—Quantitative methods

Informed by previously validated measures of implementation outcomes [28], a set of questionnaires were developed specifically for this project to assess fidelity, feasibility, and acceptance of MIAF implementation. Both caseworkers and foster families will complete these questionnaires online at different time points, including pre-placement (M1) and post-placement (M2). Regarding M1, data will be collected (a) after informative sessions for awareness raising and foster family recruitment, (b) after pre-service training, and (c) after the assessment and selection of foster families. For M2, questionnaires will be completed (d) one month following the child’s placement to assess child-foster family matching and the transition to family foster care processes, (e) at six months of placement to evaluate support during family foster care, and (d) one month following the child’s transition to a permanent solution. The number of items per questionnaire, rated on either a 3-point or 5-point scale, varies depending on the MIAF key process and informant (i.e., caseworker or foster family).

#### Process evaluation—Qualitative methods

Additionally, focus groups with caseworkers will be conducted at two stages of the research project to explore the enablers and barriers to MIAF implementation. During the first year of MIAF implementation, the focus will be on pre-placement processes (M1), while in the second year, discussions will encompass experiences related to matching, interventions during placement, and transitions in foster family care (M2). At each stage, at least three focus groups will be conducted for each participant group, with each group comprising fewer than 10 participants. The sessions will begin with an introduction to the study objectives and the participants’ role. Subsequently, informed by the framework proposed by Akin et al. [15], more in-depth questions will be asked regarding the enablers and barriers influencing MIAF implementation, including process factors, provider factors, innovation factors, client factors, organizational factors, and structural factors. All focus group discussions will be recorded, transcribed verbatim, and subjected to qualitative analysis.

Furthermore, specifically designed short semi-structured interviews will be conducted with children aged over five years. Each child will participate in an interview six months after their placement. Children will be presented with a series of open-ended questions, asked in a flexible order depending on their responses, to explore their experiences and feelings regarding foster care. The interviews will also include a warm-up drawing activity. All interviews will be audio-recorded and transcribed verbatim to facilitate qualitative data analysis.

### Outcome evaluation

The outcome evaluation will utilize a longitudinal design, gathering qualitative and quantitative data from caseworkers, foster families and children involved in the MIAF program over the initial 12 months of foster care placement. Follow-up assessments with children and their foster families are planned at 1-month (T0), serving as baseline for family and child outcomes, and subsequently at 3 (T1), 6 (T2), 9 (T3), and 12 (T4) months post-placement. Through a combination of reported and observational measures, the assessment protocol will address child development and well-being, child safety and stability, foster family well-being and the quality of relational care. Report measures will primarily be collected online, while interviews, observational measures and tasks with the child will be collected through home visits to each foster family (Table 1, for a summary of the measures and moments of data collection regarding process and outcome evaluation).

**Table 1 pone.0304244.t001:** Assessment protocol and assessment moments regarding outcome evaluation.

				Assessment Moments				
Variable	Informant		Method	T0	T1	T2	T3	T4

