### Objectives of the research study

This research, guided by the Getting To Outcomes framework [8], aims to investigate the initial implementation stage of the MIAF, a child welfare practice model recently developed to address the current national priority in child welfare policies in Portugal. The goal of the MIAF is to promote high-quality family foster care practice standards and support families and children in achieving safety, stability, and well-being outcomes. Therefore, this study seeks to conduct a mixed-method process and outcomes evaluation. In terms of process evaluation, our objectives are to (1) determine whether the MIAF is being implemented as planned (i.e., with fidelity) and assess its feasibility, appropriateness, and acceptability, and (2) identify enablers and barriers to MIAF implementation. For outcome evaluation, our objectives are to (3) describe the developmental trajectories of foster care children enrolled in the MIAF, assess their safety and stability, and (4) examine the trajectories of foster parents’ well-being and the quality of relational care. Additionally, we aim to (5) evaluate whether the MIAF mitigates the potential negative impact of early risk factors at the child (e.g., behavior problems) and family (e.g., stress, psychological symptoms) levels, measured at the time of placement, on subsequent outcomes assessed up to 12 months post-placement.

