**Family Outcomes **								
Psychological wellbeing	Foster family		Online	×		×		×
Parental stress	Foster family		Online	×		×		×
Self-efficacy in foster parenting	Foster family		Online	×		×		×
Satisfaction in foster parenting	Foster family		Online	×		×		×
Caregiver sensitive responsiveness	Caregiver-child interaction		In-person	×		×		×
Acceptance, commitment, awareness	Foster family		In-person			×		×
Retention of the foster family	Caseworkers		Online	When (and if) a child leaves care				

Note. T0 (1 month of placement), T1 (3 months of placement), T2 (6 months of placement), T3 (9 months of placement), T4 (12 months of placement).

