#### Foster family well-being and the experience of being a foster family

Caregivers will be asked to complete the Subjective Psychological Wellbeing–WHO-5 [39], which assesses *subjective psychological well-being* with 5 items, and the *Daily Hassles Questionnaire* [40], comprising 10 items to measure stress related to parenting activities. Additionally, *parental self-efficacy* and *satisfaction* concerning the foster care experience will be evaluated using the adapted version of the questionnaire Me as a Parent- Short Form (MaaP-SF) [41] and the Kansas Parental Satisfaction Scale (KPSS) [42]. The MaaP-SF consists of 4 items rated on a 5-point scale from 1 (totally disagree) to 5 (totally agree), while the KPSS comprises 3 items rated on a 7-point scale from 1 (extremely unsatisfied) to 7 (extremely satisfied). Furthermore, the intention to continue as a foster family will be assessed one month after the child has transitioned out of care.

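### Objective 5 defines risk as measured at placement, but the first measurement comes one month later, after MIAF matching and transition support; two construct labels also differ between objectives and methods

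*Protocol article*

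**What the plan says.** **Timing of risk.** In the protocol article, Objectives of the research study, objective 5 names behaviour problems as an example of child risk and gives the family side as "family (e.g., stress, psychological symptoms) levels, measured at the time of placement". The Outcome evaluation section sets the first follow-up as "planned at 1-month (T0), serving as baseline for family and child outcomes". The note to Table 1 repeats it: "T0 (1 month of placement". Table 1 starts emotional and behaviour problems, parental stress and psychological well-being at T0, with nothing before it.

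**Use of risk.** The Data analysis plan tests MIAF, with fidelity as its example, as a moderator of the path from early risk to later outcome.

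**Psychological symptoms.** The section on foster family well-being begins "Caregivers will be asked to complete the Subjective Psychological Wellbeing", meaning the 5-item WHO-5. It adds a 10-item parenting-hassles questionnaire and short scales of self-efficacy and satisfaction. None is described as measuring symptoms.

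**Appropriateness.** Objective 1 will establish fidelity and "assess its feasibility, appropriateness, and acceptability"; the abstract lists the same four constructs. The project questionnaires were built "to assess fidelity, feasibility, and acceptance of MIAF implementation". The Process evaluation section and the Discussion also name only three constructs. The former places perceived suitability under acceptability.

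**The concern.** A moderation question needs a predictor that is fixed before the moderator acts, or at least one whose timing is stated correctly. Here the objective gives one time and the schedule another, and MIAF is being delivered in between. If good early delivery lowers carer stress or child behaviour problems by the end of the first month, that benefit enters the risk variable and the moderation term cannot credit it to MIAF. If the first month goes badly, the harm appears as high initial risk.

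There is also a selection effect. A child whose placement ends in the first month has no T0 value and drops out of the objective 5 analysis. Placement breakdown is one of the stability events the study records, so this loss may be related to the outcome.

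The two label mismatches are smaller. A reader of the results could take a low WHO-5 score for a symptom measure, or look for an appropriateness result that the methods do not define.

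**Working it through.** The documents give no statistical figure to reproduce on this point, so the check sets the statements side by side.

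**1. Lag.** Stated time of risk measurement: 0 months (objective 5). Scheduled time: 1 month (Outcome evaluation; note to Table 1). Difference: 1 − 0 = 1 month. The span from T0 to T4 is 12 − 1 = 11 months, against the 12 months of placement the study sets out to cover.

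**2. Which example risks are affected.**

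| Example in objective 5 | Measure given | First taken |
|---|---|---|
| Behaviour problems | Age-specific symptom checklist, rated by the foster family | T0 |
| Stress | Parenting-hassles questionnaire, 10 items | T0 |
| Psychological symptoms | None by that name; WHO-5 well-being, 5 items, is nearest | T0 |

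So 3 of 3 are first assessed at T0 and 0 of 3 at placement. For 1 of 3 the named construct is reached only through a proxy. The Sociodemographic information section does not close the gap: it covers background data and early adversity, is collected when participation begins, and gives no date relative to placement.

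**3. What MIAF has done by T0.** The description of MIAF covers recruitment, training, assessment and selection of families, then matching, then the placement itself. The process evaluation sends out a questionnaire one month after placement about how child and family were matched and how the move into foster care went. The protocol thus treats the first month as intervention delivered and assesses that delivery at the same time point as T0. A risk score taken then comes after the exposure.

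**4. Missing risk values.** If k of the 100 planned children leave before one month, k/100 have no T0 value, so each is 1/100 = 1%. The article gives no early-exit rate, so k is unknown.

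**5. Implementation outcomes.**

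| Construct | Abstract | Objective 1 | Process evaluation | Questionnaires | Discussion |
|---|---|---|---|---|---|
| Fidelity | yes | yes | yes | yes | yes |
| Feasibility | yes | yes | yes | yes | yes |
| Acceptability | yes | yes | yes, including suitability | yes, as acceptance | yes |
| Appropriateness | yes | yes | not named | not named | not named |

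By name, 3 of 4 are carried from objective to methods.

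**The case against.** The best defence is practical. Foster carers rate the child's behaviour and the strain of their own parenting tasks, and neither can sensibly be rated on the day the child arrives. The article is also open that T0 falls at one month and serves as baseline. Both points stand. They justify the schedule, but they do not make the wording of objective 5 true.

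A second defence is that an earlier family measure would not escape MIAF either, because families are trained and selected under it. That also stands. It limits what any added measurement can achieve, and it means that no timing would give a comparison with unexposed families. Every family receives MIAF, and the Limitations section already concedes the limit on causal claims.

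A reader might go further and infer four things that the article does not support:

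- *That the risk factors are not measured.* Behaviour problems and stress are both taken at T0; they are late, not absent.
- *That carers' psychological state is not measured at all.* WHO-5 is taken at T0 and is a plausible proxy, and symptoms are given only as an example.
- *That appropriateness cannot be reported.* Suitability sits under acceptability and the items are not shown, so the two constructs may have been merged. The text shows only that appropriateness is promised separately and then not named.
- *That breakdowns in the first month go uncounted.* Caseworkers record breakdowns and retention is noted when a child leaves. Nothing starts that count at T0. What is missing for these children is the risk value.

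**Conclusion.** The timing contradiction holds in full. Objective 5 promises a predictor measured at placement, and the design delivers one measured a month later, after matching and transition support. As written, the conclusion about risk at placement is not supported for any of the three example risk factors. What can be supported is a statement about risk at one month among placements that last to T0.

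The size of any distortion cannot be worked out. It depends on how far risk scores move in the first month and how many placements end in it, and the article gives neither. The direction of the effect on the moderation estimate is open too. The point assumes only that MIAF could influence carers or children within a month, which is what its matching and transition work is meant to do.

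The symptom and appropriateness points are real mismatches between objectives and methods, but minor ones of naming and definition. The whole should be corrected because it changes what objective 5 can claim and costs little.

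**What to change.** 1. In objective 5 and in the moderation paragraph of the Data analysis plan, define child and family risk as measured one month after placement (T0).
2. Limit the objective 5 conclusion to risk at one month among placements lasting to T0, and report the number of placements that end before T0.
3. In objective 5, replace *psychological symptoms* with the construct measured, low well-being on WHO-5.
4. Either score appropriateness separately in the pre- and post-placement (M1 and M2) process questionnaires and name it in the methods, or delete it from objective 1 and the abstract.
5. Optionally, add the five WHO-5 items to the online form that follows family assessment and selection, for families who complete that form. This gives a pre-placement value for family well-being only. It still follows MIAF training and does not cover child behaviour problems or parenting stress, so it adds to items 1 and 2 and does not replace them.

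Items 1 to 3 cost wording and one reported count. Item 4 costs a scoring rule, and items if none exist, or a deletion. Item 5 costs five online questions.

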**Child Outcomes **								
Mental Development	Child		In-person	×		×		
Physical growth	Foster family		In-person	×		×		
Emotional/behavior problems	Foster family		Online	×	×	×	×	×
Well-being	Foster family		Online	×	×	×	×	×
Competence	Foster family		Online	×	×	×	×	×
Attachment disordered behaviors	Foster family		In-person			×		×
Safety and permanency	Caseworkers		Online		×	×	×	×
**Family Outcomes **								
Psychological wellbeing	Foster family		Online	×		×		×
Parental stress	Foster family		Online	×		×		×
Self-efficacy in foster parenting	Foster family		Online	×		×		×
Satisfaction in foster parenting	Foster family		Online	×		×		×
Caregiver sensitive responsiveness	Caregiver-child interaction		In-person	×		×		×
Acceptance, commitment, awareness	Foster family		In-person			×		×
Retention of the foster family	Caseworkers		Online	When (and if) a child leaves care				

Note. T0 (1 month of placement), T1 (3 months of placement), T2 (6 months of placement), T3 (9 months of placement), T4 (12 months of placement).

#### Child development and well-being

For assessing mental development, trained examiners will administer the Griffiths Mental Development Scales (0–2 and 2–8) [29]. These scales encompass six subscales: locomotor, personal and social, language, eye and hand coordination, performance, and practical reasoning (the last one only for children above 2 years). Scoring is based on reference standards that determine a functional age according to the accumulated score for each subscale. Additionally, a general quotient is obtained by averaging scores across the five subscales. For older children, cognitive ability will be evaluated using the Information and Block Design subtests of the Wechsler Preschool and Primary Scales of Intelligence (WPPSI) [30]. These subtests will provide an estimated child IQ score, following the guidelines recommended by Sattler [31]. *Physical growth* data, including height, weight, and head circumference, will be collected from the children’s medical records. Raw data will be converted into percentiles for analysis. Regarding *child emotional and behavioral problems*, foster family will be asked to complete either the Baby Pediatric Symptom Checklist for infants up to 18 months (12 items) [32], the Preschooler Pediatric Symptom Checklist for children aged 18 to 60 months (19 items) [33], or the Pediatric Symptom Checklist for school-aged children (17 items) [34], depending on the child’s age. These questionnaires are designed to assess emotional and behavioral problems in children and include questions about various types of behavior. Responses are rated on a three-point scale ranging from 0 (Not at all) to 2 (Very much), tailored to recognize behaviors typical for children in the respective age ranges. Foster families will also complete the Portuguese versions of the Secure Based Models checklists [25], which assess a child’s developmental strengths and difficulties, as an index of *well-being*. These checklists have different versions tailored to specific age ranges (i.e., 0–18 months, 19 months-4 years, 5–10 years). Items on the checklists are rated on a three-point scale: yes, sometimes, no. Additionally, caregivers are provided with open-ended questions to add any additional comments they may have. Child flourishing will also be measured using very short questionnaires consisting of either 4 items (for children aged 1–5 years, rated from 0-Never to 4-Always [35] or 5 items (for children aged 6–17 years, rated from 0-Not true to 3-definitively true [36]. *Attachment disordered behaviors* will be assessed using The Disturbances of Attachment Interview (DAI) [37], a semi-structured interview administered to the foster family. The DAI aims to gather information about the symptoms of Reactive Attachment Disorder and Disinhibited Social Engagement Disorder. It consists of 12 items, each coded on a scale of 0 (rarely or minimally), 1 (sometimes or somewhat), or 2 (clearly), based on the severity and frequency of behaviors described by the caregiver.

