### Overview of the research design

The research project employs a multi-method approach, incorporating both qualitative and quantitative data collection methods, along with a multi-informant approach. Process evaluation data for the MIAF key processes will be collected at two points: pre-placement (M1) and post-placement (M2). Outcome evaluation data will be collected longitudinally over the first 12 months of the child’s placement in foster care. The study will recruit 25 caseworkers engaged in implementing the MIAF from four child welfare agencies situated in the north and south of Portugal. Additionally, 100 children aged 0–9 years entering foster care and their respective foster families receiving the MIAF will be included in the study. It is expected that this sample will cover nearly the entire population served by the four foster care agencies participating in the study. The recruitment period for participants will extend from March 2024 until December 2025.

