#### Sociodemographic information

Sociodemographic data of caseworkers (e.g., years of experience), children (e.g., age and sex; but also, e.g. exposure to early adversities, such as neglect and abuse) and their foster families (e.g., duration of fostering experience, number of children they are fostering) will be collected at the beginning of their participation in the study.

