### Data analysis plan

The project will gather a comprehensive dataset, requiring an analytical strategy that encompasses both qualitative and quantitative data analysis techniques. For qualitative data analysis, we will employ thematic analysis using a deductive-inductive approach, grounded in theoretical and empirical knowledge on the topic. We will follow recommended guidelines for coding, such as the Braun and Clarke step-based approach [47], and reporting, such as the Consolidated Criteria for Reporting Qualitative Research (COREQ) Checklist. Qualitative analysis will be facilitated using software such as NVivo and MAXQDA.

Regarding quantitative data, diverse analytical approaches will be employed. Descriptive analysis will examine demographic characteristics and study variables, presenting mean ± standard deviation (SD) for continuous variables and frequencies (n) and percentages for categorical variables. Correlational analysis will use Spearman and Pearson correlations, while the chi-square test will assess nominal variables. Growth Curve Modeling will examine the developmental trajectories of children in family foster care by analyzing their initial status and considering time-varying predictors (e.g., early adverse experiences, quality of care). Additionally, trajectories of family well-being will be examined. Moderation analyses will examine the influence of the MIAF (e.g., fidelity) on the relationship between predictors and outcome variables. Specifically, these analyses will explore the moderating effect of the MIAF model on the relationship between early child and family risk factors and subsequent outcomes. Statistical significance will be set at *p* < 0.05. Quantitative analysis will utilize software such as SPSS version 29.0 (SPSS Inc., Chicago, IL, USA) and R Statistics.

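### Analysing height, weight and head circumference as percentiles gives equal growth gains unequal weight and makes apparent change depend on starting size

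*Protocol article*

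**What the plan says.** In the protocol article, the section on child development and well-being says that physical growth "data, including height, weight, and head circumference, will be collected from the children’s medical records", followed by: "Raw data will be converted into percentiles for analysis". The last two words set percentiles as the scale of analysis, not only of presentation. The article mentions no z-score or SD score and no later transformation of the percentiles.

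Table 1 lists "Physical growth" among the child outcomes, with marks at T0 (1 month of placement) and T2 (6 months) only.

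The data analysis plan gives mean and SD for continuous variables, Spearman and Pearson correlations, and growth models for the children: "Growth Curve Modeling will examine the developmental trajectories of children in family foster care by analyzing their initial status". It names early adverse experiences among the predictors. These analyses serve the third objective, to "describe the developmental trajectories of foster care children enrolled in the MIAF". The planned sample is 100 children aged 0–9 years. The section on sociodemographic information says that each child's "exposure to early adversities, such as neglect and abuse" will be recorded.

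**The concern.** Mean change, Pearson correlation and growth curve models all treat a difference of a given number of units as the same amount wherever it falls on the scale. Percentiles lack that property. They run from 0 to 100 and follow the cumulative distribution of the reference, so a fixed gain in SD units is many points near the median and few in the tails.

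Two things follow for change from T0 to T2.

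- The average is driven mainly by children who start near the middle of the reference, and the smallest children add little to it even if they grow as well.
- Apparent change depends on starting size through the scale alone. If children with more early adversity also start smaller, which is an assumption here, adversity could appear to predict poorer growth when the true gain is identical.

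**Working it through.** **Inputs.** From the protocol article: percentile scale for analysis; T0 and T2 as the growth assessments; 100 children; significance level 0.05. The article gives no baseline growth, expected gain, or sample-size or power figure for growth, so there is no stated figure to reproduce. Assumed: a normal reference, starting z-scores from 0 to -3, and gains of 0.25, 0.5 and 1 SD.

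**Step 1: convert.** Percentile = 100 × Φ(z), where Φ is the standard normal distribution function. For a gain d from start z, the change in percentile points is 100 × [Φ(z + d) − Φ(z)].

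| Start z | Start percentile | Gain 0.25 SD | Gain 0.5 SD | Gain 1 SD |
|---|---|---|---|---|
| 0 | 50.0 | 9.9 | 19.1 | 34.1 |
| -1 | 15.9 | 6.8 | 15.0 | 34.1 |
| -2 | 2.3 | 1.7 | 4.4 | 13.6 |
| -2.5 | 0.62 | 0.60 | 1.7 | 6.1 |
| -3 | 0.13 | 0.16 | 0.49 | 2.1 |

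Example: from z = -2, a 0.5 SD gain is 100 × [Φ(-1.5) − Φ(-2)] = 6.68 − 2.28 = 4.4 points.

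**Step 2: compare.** Relative to a start at the median, a 0.5 SD gain is recorded as smaller by a factor of 19.15/14.99 = 1.3 at z = -1, 19.15/4.41 = 4.3 at z = -2, 11.6 at z = -2.5 and 39 at z = -3. For a 1 SD gain the factors are 1.0 at z = -1, 34.1/13.6 = 2.5 at z = -2 and 34.1/2.14 = 16 at z = -3. On z-scores each factor is 1.

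**Step 3: effect on a test of mean change.** An illustrative simulation used a paired t-test with n = 100, baseline SD 1, SD of change 0.5 and 4,000 runs per setting. All of these except n are assumptions.

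| Pattern of gain | Baseline mean z | Power, z-scores | Power, percentiles |
|---|---|---|---|
| Only below z = -1 (0.25 × shortfall) | -1 | 48% | 35% |
| Only below z = -1 (0.25 × shortfall) | -1.5 | 91% | 65% |
| Same 0.12 SD for every child | 0 | 66% | 59% |
| Same 0.12 SD for every child | -0.5 | 66% | 76% |
| Same 0.12 SD for every child | -1 | 67% | 86% |

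Percentiles lose power when catch-up is concentrated in the smallest children. They do not when all children gain equally and the cohort starts below the median.

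**Step 4: read the last rows with care.** Below the median the percentile curve is convex, so random change alone raises the mean percentile. If z is normal with mean m and variance v, the mean percentile is 100 × Φ(m/√(1 + v)). In the simulation v is 1 at T0 and 1 + 0.5² = 1.25 at T2. At m = -1 with no true gain, the mean moves from 100 × Φ(-1/√2) = 23.98 to 100 × Φ(-1/1.5) = 25.25, or 1.27 points. With the 0.12 SD gain it moves to 100 × Φ(-0.88/1.5) = 27.87, or 3.9 points. About a third of the apparent gain (1.27/3.9) is thus produced by the scale. This rests on the assumed increase in variance from T0 to T2.

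**The case against.** The case for leaving the sentence alone has several fair parts.

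- *The worst case is not typical.* A 1 SD gain centred on the median, from z = -0.5 to 0.5, is 38.3 points, about 18 times the 2.1 points for z = -3 to -2. But only 0.13% of a reference population lies below z = -3. From z = -2 to -1 the ratio is 38.3/13.6 = 2.8. This stands, and a range of starts should be shown. Nothing in the article supports a gain as large as 1 SD in the five months between T0 and T2.
- *The share of very small children is unknown.* A reader might infer from the recording of neglect and abuse that many children will start in the low tail. The article says only that exposure will be recorded. It gives no baseline growth distribution. This stands.
- *Growth recovery in the most deprived children is not a stated objective.* The introduction mentions recovery after placement as background, and the objective is to describe developmental trajectories. Growth is one of seven child-outcome rows in Table 1, and no primary outcome is named. This stands and limits the reach of the point.
- *Some planned analyses are unharmed.* Spearman correlations at one time do not change under a monotone conversion. The plan does not assign growth curve models to physical growth by name, and with two assessments such a model is little more than a change score. Both remarks are right, but a change score in percentiles has the same distortion.
- *The choice is reversible.* Raw measurements are collected, so z-scores can be computed later. True, and this is a reason to correct the sentence now at no cost.

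The objection that this is detail left to a fuller analysis plan does not stand, because the article itself fixes the scale for analysis.

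**Conclusion.** The point holds as an ill-chosen analysis scale for one outcome. Under a normal reference, equal gains receive unequal weight: a 0.5 SD gain is recorded as 19.1 points at the median, 4.4 at z = -2 and 0.5 at z = -3. Compression is mild at z = -1, strong at about z = -2, and close to complete only at about z = -2.5 or below.

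A reader might go further and conclude that percentiles will hide catch-up in this cohort generally, or that they always cost power. The article supports neither. The first depends on how many children start very low, which is not given. The second depends on the pattern of gain, and the simulation shows both directions. What holds without knowing the cohort is that mean change and Pearson correlations on percentiles mix true growth with starting size. This is a worthwhile improvement to a secondary part of the plan and does not threaten the study as a whole.

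**What to change.** In the section on child development and well-being, replace the sentence on percentiles with: 'Raw data will be converted into age- and sex-standardised z-scores (SD scores) for analysis; percentiles will be reported for description only.'

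The cost is one sentence. The same medical-record measurements serve, and z-scores need the same kind of growth reference that percentiles already require. No visit, participant or measurement is added, and the change can be made at any time before analysis.
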